### Statistical power calculation

In a previous study from our group on affective cognition in high-risk pregnant women, 50% went on to develop PPD [15]. On average, these women rated infant cries 0.47 standard deviations *more negatively* than high-risk women who remained healthy. Hence, 83% of high-risk women who went on to develop PPD, exhibited a negative bias in their responses to infant cries during pregnancy compared with 48% high-risk women who remained healthy. Therefore, targeting negative affective cognitive response to infant emotion may reduce the risk of PPD. Based on this PPD incidence of 50% [15], we aim to demonstrate a clinically significant reduction of the incidence of PPD from 50 to 25% (i.e. reducing the risk to half). To reach a statistical power of ≥ 80% for detecting this effect at a two-sided 0.05 alpha level, we need a sample of *n* = 58 pregnant high-risk women with complete data per intervention arm (https://clincalc.com/stats/samplesize.com). To accommodate for an expected dropout rate of up to 20% (as in our pilot study), we aim to include *n* = 73 women per treatment arm, i.e. *N* = 146 trial participants in total.

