### Randomization

Pregnant PPD high-risk women are randomized to PACT or care as usual (CAU) using the REDCap randomization module. We stratify randomization with age (above/below 30 years) and parity (primiparous v. multiparous). A researcher outside the group generated the allocation sequence by creating an allocation table with allocation in blocks of varying size using Sealed Envelope Ltd [52]. This allocation table is used by REDCap’s randomization module. The postdoc on the project conducts the randomization. Allocation concealment will be ensured as REDCap will not release the randomization code until the patient has been recruited into the trial and the “randomize button” in REDcap has been selected.

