### Procedure

At baseline (T0), all pregnant women undergo a comprehensive (2-h) assessment of affective cognitive processing of infant stimuli and non-emotional cognition, clinical rating of depressive symptoms, and completion of questionnaires regarding attachment to the unborn child, bonding to own parents, emotional relationship with their partner, demographics, clinical history, and state- and trait anxiety (details below). Further, a hair sample is collected from women to assess cortisol levels as a biological measure of stress. Based on the responses on questionnaires and affective cognitive processing, pregnant women are categorised as either at high or low risk of developing PPD (see the “In- and exclusion criteria” section above for specific inclusion criteria for high- and low-risk groups, respectively). High-risk participants are randomized to either PACT or CAU immediately after the baseline testing. Participants in the active intervention group complete a total of five individual training sessions over a period of approximately 5 weeks (for details on the study design, see Fig. 2). Around 5-6 weeks after the baseline assessment, all high-risk pregnant women (in the PACT or CAU arms) undergo their second assessment (T1) of affective cognition and self-ratings, including attachment feelings to the unborn child. For women receiving PACT, this assessment takes place within 1 week after the fifth training session. Lastly, if they have not given birth yet, women in the intervention group are offered a *booster* training session approximately 6-8 weeks after their baseline assessment. If participants face challenges attending in-person sessions, for example due to the late stage of their pregnancy, we will offer to conduct two sessions over the telephone or an online meeting. While computer training will not be feasible in this format, we will emphasize the key points from previous sessions and guide them on how to maintain their progress through home-based exercises like mindfulness techniques.

One week after their due dates, participants receive an e-mail with a link to 5-min online questionnaires regarding the birth, the infant’s health and well-being and mothers’ potential experience of depressive symptoms. On a weekly basis during the first 6 weeks after giving birth, mothers receive links to an online questionnaire to assess their depressive symptoms.

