### Statistical analyses

Group differences in the prevalence of PPD will be analysed with generalized mixed model and linear mixed models, respectively. Group differences in affective cognitive changes from baseline to follow-up (in pregnancy) will be analysed with linear mixed models. We will apply appropriate imputation methods before fitting the model to address missing data concerns. With mediation analyses, we will investigate if depressive symptoms and the prevalence of PPD after birth are mediated by changes in affective cognition. Associations between affective cognitive performance on training tasks and changes in affective cognitive outcomes and PPD prevalence will be explored with regression analyses. All analyses will involve adjustment for variables on which participants may differ at baseline, including socio-demographic factors, attachment feelings to the unborn child, child gender, clinical history, and depressive symptoms during pregnancy. We will use the SPIRIT reporting guidelines [74].

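### The covariate rule ties adjustment in all analyses to possible baseline differences, leaves the primary model open and does not commit to the stratification factors

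*Protocol article*

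**What the plan says.** The rule is in Methods, Statistical analyses: "All analyses will involve adjustment for variables on which participants may differ at baseline". Five domains follow, introduced as examples: socio-demographic factors, attachment to the unborn child, child gender, clinical history, and depressive symptoms in pregnancy. Because the sentence covers all analyses, it covers the primary one, PPD yes or no over six months after birth, for which the section names a generalized mixed model.

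The Randomization section says: "We stratify randomization with age (above/below 30 years) and parity (primiparous v. multiparous". The Statistical analyses section does not mention these two factors as model terms.

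On timing, the Procedure section has all high-risk women, about 5 to 6 weeks after baseline, "undergo their second assessment (T1) of affective cognition and self-ratings, including attachment feelings to the unborn child". That visit falls after randomisation.

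The sample size rests on an unadjusted comparison of two proportions: a "reduction of the incidence of PPD from 50 to 25" percent, a "two-sided 0.05 alpha level", and a "statistical power of ≥ 80" percent. This gives "58 pregnant high-risk women with complete data per intervention arm", raised to 73 for "an expected dropout rate of up to 20" percent.

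**The concern.** Randomisation makes any baseline difference between arms a chance event. A covariate earns its place by predicting the outcome or by having been used to stratify, not because the arms happen to differ on it. A rule built on difference points the analyst to the wrong criterion.

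The rule also fails to close the set. The list is illustrative, its entries are domains rather than variables, and nothing says what counts as a difference. Several primary models, with different p-values, would all comply with the sentence.

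The design used age and parity to balance the arms, but the analysis text does not carry them forward. Parity is unnamed, and age is present only if one reads it into socio-demographic factors. Omitting a stratification factor that predicts the outcome makes the test somewhat conservative.

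Last, depressive symptoms and attachment carry no visit label. Attachment exists at both T0 and T1, and the Intervention section describes a visualisation task meant to foster bonding with the unborn child and reduce depression. A T1 value could therefore lie on the path from treatment to outcome, and adjusting for it would change the question being answered.

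**Working it through.** **1. The plan's own figure.** Inputs from Statistical power calculation: p1 = 0.50, p2 = 0.25, two-sided alpha 0.05, power 0.80. The mean proportion is 0.375. With pooled variance and no continuity correction:

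n = [1.960 × √(2 × 0.375 × 0.625) + 0.842 × √(0.50 × 0.50 + 0.25 × 0.75)]² / 0.25²
= [1.342 + 0.557]² / 0.0625 = 57.7, so 58 per arm.

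Dropout: 58 / 0.80 = 72.5, so 73 per arm and 146 in total. Power at 58 per arm is 80.2%. The stated figures reproduce, and they need no covariate.

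**2. What leaving out age and parity costs.** The documents give no prognostic strength for either factor, so a range is assumed: odds ratio 1, 1.5, 2 or 3 for each, with each factor splitting the women in half. Simulated trials had 116 evaluable women, allocation balanced within the four age-by-parity strata, marginal rates of 50% and 25% (50% in both arms for type I error), and a Wald test from logistic regression. There were 6,000 runs per setting; the Monte Carlo standard error is about 0.5 points for power and 0.3 for type I error.

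| Assumed odds ratio per factor | Power without / with the factors | Type I error without / with |
|---|---|---|
| 1 | 80.2% / 80.4% | 5.0% / 5.0% |
| 1.5 | 80.3% / 81.2% | 4.3% / 4.4% |
| 2 | 80.4% / 82.2% | 4.8% / 5.3% |
| 3 | 80.4% / 84.1% | 3.9% / 5.3% |

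The gain runs from 0.2 to 3.7 points, so about 0 to 4. Power without the factors stays at 80% throughout. At odds ratio 3 the unadjusted test falls below its nominal level (3.9%), which accounts for part of the difference in power. The 4.3% at odds ratio 1.5 appears with and without the factors, so it is not an effect of omitting them.

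**3. What an open set allows.** Assumed: one independent, normally distributed covariate for each of the five listed domains, odds ratio 1, 1.5 or 2 per SD, 58 women per arm, no treatment effect. Five covariates give 2⁵ = 32 possible sets. There were 1,500 runs per setting, with a standard error of about 0.5 to 0.9 points.

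| Assumed odds ratio per SD | Fixed full set | Only covariates imbalanced at p < 0.10 | Smallest p over 32 sets |
|---|---|---|---|
| 1 | 5.1% | 4.7% | 7.0% |
| 1.5 | 5.2% | 4.5% | 10.9% |
| 2 | 4.9% | 3.5% | 14.3% |

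A fixed set holds the level. Selection on imbalance, applied mechanically, does not inflate it. Inflation appears only when the set is chosen for its result.

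**4. Timing.** No size is attached to the T1 question. The documents give neither the effect of PACT on T1 attachment or symptoms nor how strongly those values predict PPD.

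**The case against.** The wording can be read more kindly. It refers to participants rather than arms, describes no test of baseline balance, and may simply be a list of plausible prognostic domains named in advance. It may also be meant for the risk-factor work across all pregnant women described under Aims and hypotheses, where high-risk and low-risk women differ for reasons other than chance. And this is a condensed article: exact covariates, stratification terms and score timing commonly belong in an analysis plan that is not shown.

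Much of this stands. The text does not show that covariates would be picked after looking at the arms. Socio-demographic factors ordinarily include age, so only parity is clearly unnamed. Depressive symptoms are already listed, so any precision they bring cannot be counted as lost. The governing phrase refers to baseline, so adjustment for T1 values is a possibility the text leaves open, not the plan.

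The objection does not rescue the sentence. The article states a rule, applies it to every analysis and ties it to difference. An analysis plan that fixed a proper primary model would have to depart from that rule, not merely add detail. Even on the kinder reading, an illustrative list of domains does not define a model.

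**Conclusion.** The point holds as a badly fixed analysis rule. The criterion for adjustment is the wrong one for a randomised comparison, the primary model is left open, the stratification factors are not carried into it, and two listed covariates are not explicitly tied to T0.

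Its size is modest. Including age stratum and parity adds about 0 to 4 points of power and avoids a slightly conservative test if both are strongly prognostic. This rests on the assumed odds ratios of 1 to 3. The larger exposure is the open set: a type I error of up to about 7 to 14%, against about 5% for a fixed set, under the assumption of five independent covariates with odds ratios of 1 to 2 per SD.

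A reader might infer more than the documents support:

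- That the trial is underpowered as a result. It is not; the unadjusted comparison keeps its planned 80%.
- That adjusting for imbalanced covariates inflates type I error. It gave 3.5 to 4.7% here; its faults are dependence on the data and a poor criterion.
- That 7 to 14% is the expected error rate. It is the worst case of deliberately choosing the most favourable set, which the protocol does not describe.
- That the effect will be biased towards no difference by T1 adjustment. Nothing says T1 values will be used as covariates.

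This is a free improvement.

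**What to change.** Replace the baseline-difference rule with a fixed primary model containing:

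- arm;
- age stratum (above/below 30 years);
- parity (primiparous or multiparous);
- one named T0 depressive-symptom score, for example the T0 EPDS. Only one should be named, so that the choice is closed. The T0 HDRS-6 is also available, but its range is cut at entry because women scoring 9 or more are postponed or excluded.

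Fix the list before outcomes are compared by arm. State that covariates are T0 values only, that none is chosen by comparing the arms at baseline, and that no post-randomisation value enters a treatment-effect model except as the mediator in the planned mediation analyses. That exception is needed because the second hypothesis depends on change measured at T1.

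Keep the longer list for one sensitivity analysis, with each domain replaced by named variables. Child gender can stay there even if recorded after birth, since it is settled before randomisation. If the baseline-difference wording was meant for the comparison of high-risk and low-risk women, confine it to that analysis.

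The cost is wording only. Age and parity are used at randomisation, and both symptom scores are collected at T0, so nothing new is measured and the sample size is unchanged.

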## Background and aim

Postpartum depression (PPD) is a severe mental illness with a prevalence of around 8% for women with no history of depression [1, 2] and 30–50% for women with a history of previous depression or bipolar disorder (mania and depression) [3–7]. Multiple factors are associated with risk of PPD, including a history of depression, unwanted pregnancy, low emotional support, low socio-economic status [8] pregnancy complications [4, 9–11], weak attachment feelings to the unborn child [12, 13], and emotion regulation difficulties [14]. Emerging evidence indicates that negative cognitive bias in the perception of infant cues and reactivity to infant distress plays a key role for the risk of PPD. For example, we showed that more negative ratings of infant crying during pregnancy were associated with a substantially increased risk of PPD with an odds ratio of 3.75 [15]. This finding is in line with evidence that negative cognitive bias is a risk and maintaining factor for depressive episodes [16, 17]. Pregnant women at known risk of PPD are commonly offered prophylactic *pharmacologic* interventions, most commonly with selective serotonin reuptake inhibitors (SSRIs) [18]. However, many pregnant women are reluctant to accept pharmacological interventions due to their potentially harmful effects on the foetus [19–21]. Psychological interventions, including talk therapy, psychoeducation, and midwife consultations, have been found to reduce PPD symptoms [22–26]. However, these interventions generally focus on *detecting and treating* rather than *preventing* PPD [27]. *Psychological preventive* strategies in pregnant women *before* PPD onset are thus urgently needed.

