### In- and exclusion criteria

General inclusion criteria are second or third trimester pregnancy, age ≥ 18 years, and ability to speak and read Danish. Inclusion criteria for the high-risk pregnant group are either negative cognitive bias in emotional reactivity to infant distress (cut-off ≥ 96 on a scale from 0 to 100) *or* high-risk status according to the Antenatal Risk Questionnaire (ANRQ). The ANRQ assesses specific key psycho-social risk factors that increase the risk of developing PPD and considers pregnant women at high risk of PPD if they a) have a personal history of severe mental illness, b) have experienced childhood emotional, physical, or sexual abuse or c) if their total score on psycho-social risk factors is above the cut-off (> 23). Pregnant women diagnosed with a personality disorder will be excluded from randomization due to their higher treatment resistance [50]. However, they will still be included at baseline and follow-up after birth to explore the risk factors that predict PPD. Inclusion criteria for the low-risk pregnant group are the absence of a personal or family history of mental illness, the absence of negative bias and three or less of the additional risk factors mentioned above. General exclusion criteria are schizophrenia and current substance use disorder. Additionally, participants who have a score of 9 or more on the Hamilton Depression Rating Scale-6 items (HDRS-6), indicating moderate depression [51], will be postponed or excluded. This criterion is crucial for our prevention-focused approach, ensuring participants without active depression, allowing us to prioritize prevention over treatment.

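### The T0 infant-cry/distress rating, the strongest PPD predictor quantified within high-risk women, is not pre-specified as a covariate for the primary analysis

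*Protocol article*

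**What the plan says.** The Statistical analyses section gives one adjustment rule for every analysis: "All analyses will involve adjustment for variables on which participants may differ at baseline", followed by the examples "including socio-demographic factors, attachment feelings to the unborn child, child gender, clinical history, and depressive symptoms during pregnancy". The baseline response to infant cries is not among them.

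Elsewhere the article treats that response as prognostic:

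- Background and aim: it was "associated with a substantially increased risk of PPD with an odds ratio of 3.75".
- Statistical power calculation: in an earlier study of high-risk women by the same group, those who developed PPD rated cries 0.47 SD more negatively than those who stayed well. Also, "83% of high-risk women who went on to develop PPD, exhibited a negative bias in their responses to infant cries during pregnancy", against 48% of those who stayed well.

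The measure is in hand before allocation. The Procedure section has all women assessed on affective cognition at T0, with high-risk women randomised straight afterwards. The eligibility section makes one entry route "negative cognitive bias in emotional reactivity to infant distress (cut-off ≥ 96 on a scale from 0 to 100"); the other is high-risk status on the ANRQ. Randomisation is stratified by age (30 years) and parity only.

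**The concern.** The trial's rationale is that negative responses to infant distress in pregnancy raise the risk of PPD. A statistician would therefore expect the baseline value of that response to head the covariate list for the PPD comparison. Because there are two entry routes, women with and without the bias are mixed in the randomised sample, and nothing in the allocation balances them.

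Two things are at stake. One is power: the design sits at about 80% with no reserve, and adjusting for a prognostic baseline variable already collected is free. The other is pre-specification: a rule that covers variables on which participants may differ neither commits the sponsor to this covariate nor prevents the choice from being made after baseline differences are seen.

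The T0 rating precedes randomisation. It is not the T0-to-T1 change that the mediation analysis uses, so adjusting for it does not remove any of the treatment effect.

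**Working it through.** **Inputs.** From Statistical power calculation: PPD 50% v 25%, two-sided 0.05, power at least 80%, 58 complete cases per arm, 20% dropout, 73 randomised per arm; strength of the predictor 0.47 SD, or 83% v 48%. From Background and aim: PPD in 30–50% of women with a history of depression or bipolar disorder, 8% with no history of depression.

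**The plan's own figure.** Two proportions, pooled variance, no continuity correction: 58 per arm, power 80.2%. 58/0.80 = 72.5, so 73. Both figures reproduce.

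**Rank of the predictor.**
- Bias: stated OR 3.75; from 83% v 48%, (0.83/0.17)/(0.48/0.52) = 5.3.
- History: 30% v 8% gives (0.30/0.70)/(0.08/0.92) = 4.9; 50% v 8% gives 11.5.

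Bias is therefore not clearly the strongest predictor overall. It is the strongest one quantified within high-risk women.

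**Outcome variance explained.**
- Continuous rating, d = 0.47: R² = d²/(d² + 4) = 0.2209/4.2209 = 0.052.
- Yes/no bias at 50% PPD: prevalence 0.5×0.83 + 0.5×0.48 = 0.655; PPD risk 0.415/0.655 = 63.4% with bias and 0.085/0.345 = 24.6% without, a difference of 0.387; R² = 0.655×0.345×0.387²/0.25 = 0.136.
- Normal separation implied by 83% v 48%: d about 1.00, R² = 0.20.

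Under normality with equal SDs, 0.47 SD and 48% would imply about 66% in cases, not 83%. The two reported strengths do not match, so only a range can be given.

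**Power at 58 per arm**

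| Strength used | Method | Unadjusted | Adjusted |
|---|---|---|---|
| 0.47 SD | effective n = 58/(1 − R²) | 80.2% | 82.3% |
| 0.47 SD | simulated logistic | 81.8% | 83.9% |
| 83%/48%, yes/no | effective n | 80.2% | 85.7% |
| 83%/48%, yes/no; PACT halves risk in all women | simulated linear risk difference | 80.1% | 83.7% |
| 83%/48%, yes/no; PACT acts only through bias | simulated linear risk difference | 79.7% | 81.6% |
| 83%/48% as about 1.00 SD | effective n | 80.2% | 88.3% |
| 83%/48% as about 1.00 SD | simulated logistic | 80.3% | 88.2% |

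The logistic runs used 4,000 trials each and the linear runs 20,000. In the linear runs, adjustment cut the variance of the risk difference by 8% (halving), 3% (bias only) and 12% (no effect), with adjusted type I error 0.051.

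**Scale.** In the logistic runs the SE of the treatment log-OR rose with adjustment (0.408 to 0.425; 0.407 to 0.475), while the log-OR moved further from zero (−1.14 to −1.20; −1.12 to −1.43). The gain on that scale is in power.

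**Chance imbalance at 58 per arm.**
- Continuous: the SD of the standardised arm difference is √(2/58) = 0.186, so a difference above 0.2 SD in either direction has probability 28%. The risk slope per SD is √0.052×0.5 = 0.114. A 1-in-20 imbalance shifts the risk difference by 1.96×0.186×0.114 = 4.2 points.
- Yes/no: SD √(2×0.655×0.345/58) = 8.8 points; shift 1.96×0.088×0.387 = 6.7 points.

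Against the 25-point target these are about 17% and 27%.

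**The case against.** The strongest reply is that the list is illustrative. The governing clause covers any variable on which participants may differ at baseline, and the baseline rating is such a variable. A reader might infer from the named examples that it is excluded, or that the model could do nothing about an imbalance in it; the text supports neither. Exact covariates are also normally settled in a SAP, which is not shown. This stands as far as it goes: the rating is unnamed, not ruled out. What remains is that the article does state a covariate rule, and the rule as worded leaves this variable to later choice.

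A reader might also take bias to be the strongest predictor in the whole article. The figures for history of depression or bipolar disorder contradict that, and clinical history is already on the list.

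The size is fairly challenged too. For a continuous covariate, 0.47 SD is the matching figure, worth about 2 points of power. The 83%/48% figures come from another cohort, and the article does not say that its definition of negative bias equals the cut-off of 96 used here. Every randomised woman without bias has entered through the ANRQ, which may weaken the association. The calculations include none of the covariates already named.

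Finally, a chance imbalance does not bias a randomised comparison on average, and the unadjusted standard error already allows for it.

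**Conclusion.** The point holds in a limited form. The covariate with the best quantified prognostic value in the randomised population is available for every woman before allocation, is not a stratification factor, and is not pre-specified for the primary PPD analysis.

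The expected gain is about 2 points of power on the 0.47 SD figure and about 2 to 8 points on the 83%/48% figures, depending on the model and on how PACT acts. These are upper bounds, for the reasons of overlap and selection given above. They assume that the eligibility rating in this trial behaves like the cry rating in the earlier study.

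Two stronger conclusions should not be drawn. The plan does not give up a narrower interval if the model is logistic, since the SE of the log odds ratio does not fall. Nor would leaving the rating out make the comparison biased: the 4 to 7 point shift describes an unlucky realised imbalance, which adjustment corrects conditionally. The weakness is inexpensive to remove and should be removed, but it does not threaten the validity of the trial.

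**What to change.** Before unblinding, state in the SAP or a protocol update that the continuous T0 rating of infant cry/distress (the eligibility measure) is a fixed covariate in the primary PPD model and in the model for weekly depressive symptoms, whatever baseline imbalance is observed.

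The cost is one line of analysis text, with no new data and no change to conduct. Dropping child gender to keep the model the same size is optional and not part of this recommendation.
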